###### Non-inclusion criteria

- Patient refusing the study.

###### Conduct of the research

Eligible patients are selected from the computerized database of the diabetes department of the CHSF, over the period 2017-2019. Eligibility criteria are then verified in the patient record.

After sending the information form to the patients and respecting the no-objection period, the patients will be included in the study and the data collection will be performed.

The data are collected from the patient records, and are recorded on a computer medium.

Each patient will be assigned a group, either the experimental group or the control group. The 2 groups will be defined according to the number of consultations honored each year over a 2-year period Patients who have honored at least an average of 2 consultations per year for 2 years, i.e. 4 sessions over 2 years at least, will be included in the experimental groupPatients who do not reach this number will be included in the control group.

t0/14

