#### Primary outcome

Foot wound recurrence at 2 years

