###### Study population

- - 1. **Inclusion criteria**
- Patient with a type 1 or 2 follow-up at the Centre Hospitalier Sud-FranciIien (CHSF),
- Discharge from hospital from a foot wound between 2017 and 2019 with a 2 years post-healing follow-up
- Age greater than or equal to 18 years,
- People not deprived of liberty,
- Subject informed of the study and did not object.

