###### Nature of data collected

- Verification of inclusion criteria

- Age and gender

- Type and duration of diabetes

- Presence of arterial disease, diabetic neuropathy

- History of amputation

- HbAlC

During the 2-year observation period from the date of recovery:

- Number of follow-up visits honored over a two-year period from the time of healing

- Recurrence of foot wounds Hospitalization for foot wounds

- Pedicure follow-up

- Appropriate footwear.

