###### Description of the statistical methods

The 2 groups will be defined according to the number of consultations honored each year over a 2-year period. Patients who have attended at least an average of 2 consultations per year for 2 years, i.e. a minimum of 4 sessions over 2 years, will be included in the experimental group Patients who do not reach this number will be included in the control group.

The categorical variables will be presented by their numbers and percentages, and compared by Fisher's exact tests or chi2. Quantitative variables will be presented by their median and interquartile range, or by their mean and standard deviation, and compared by t-tests or Wilcoxon tests, depending on their distribution

The rates of recurrence, hospitalization, pedicure follow-up and adapted footwear will be compared between the 2 groups by Fisher exact tests.

The time to recurrence in each group will be measured by the Kaplan-Meier estimator, and compared between the 2 groups by a log-rank test. If the conditions for application are met, the time to recurrence will be analyzed by a multivariate Cox regression model taking into account the characteristics of the patients (age, sex, length of diabetes, presence of arterial disease, neuropathy) as well as whether or not they were followed up in a "foot in remission" consultation, whether they had pedicures and whether they wore adapted shoes.

The results of the multivariate Cox regression study took into account the characteristics of the patients (age, sex, length of diabetes, presence of arterial disease, neuropathy) as well as whether or not they were followed up in a "foot in remission" consultation, whether or not they had received pedicure and whether or not they wore adapted shoes.

All tests will be performed in a two-sided manner, with a 1st species risk alpha fixed at 5%. The statistical analysis will be performed by [name] of the Clinical Research Unit of the CHSF, using the R software (R Core Team (2021). R: A language and environment for statistical computing. R Foundation for Statistical Computing, Vienna, Austria. [https://www.R-project.org/](http://www.R-project.org/))).

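### Groups are defined by visits counted over the same 2 years as recurrence, so the comparison is biased whenever recurrence changes attendance

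*Protocol*

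**What the plan says.** All references are to the Protocol.

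- **Grouping.** Conduct of the research defines the experimental group as "Patients who have honored at least an average of 2 consultations per year for 2 years, i.e. 4 sessions over 2 years at least"; everyone else is a control. Description of the statistical methods repeats the rule.
- **Exposure window.** Nature of data collected lists "Number of follow-up visits honored over a two-year period from the time of healing".
- **Outcome window.** That item and recurrence both stand under the lead-in "During the 2-year observation period from the date of recovery". The primary outcome is "Foot wound recurrence at 2 years".
- **Follow-up.** Inclusion requires discharge after a foot wound "with a 2 years post-healing follow-up".
- **Tests.** "The rates of recurrence, hospitalization, pedicure follow-up and adapted footwear will be compared between the 2 groups by Fisher exact tests". Also: "The time to recurrence in each group will be measured by the Kaplan-Meier estimator, and compared between the 2 groups by a log-rank test".
- **Cox model.** If its conditions are met, a Cox model adds patient characteristics, a yes/no term for follow-up in the remission consultation, pedicure care and adapted shoes.

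The protocol states no landmark, no time-dependent exposure, no restriction to visits before recurrence, and no rule for visits made because of a recurrence.

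**The concern.** Time to recurrence starts at healing, but a patient's group can depend on visits made up to month 24, including those after the outcome has occurred. The comparison therefore mixes two things: the effect of visits on recurrence, which is the primary objective, and the effect of recurrence on visits, which is not.

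The direction depends on what recurrence does to counted attendance. If it takes patients out of the remission consultation, or if later visits are not counted, patients who recur early tend to fall into the control group and the follow-up looks protective. In the extreme case this is immortal time. If a recurrence generates extra counted visits, patients who recur are moved into the experimental group and the follow-up looks harmful, which is reverse causation. A positive result could not be read as benefit, and a real benefit could be masked or reversed.

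**Working it through.** The protocol gives no power or sample-size figure to reproduce, so the check asks what the stated rule yields when visits have no effect on recurrence.

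**Step 1: one patient, by hand.** Assume visits follow a Poisson process at 2 per year and the patient recurs at month 6. The expected count over 2 years is 2 × 0.5 + 2 × m × 1.5 = 1 + 3m, where m multiplies the visit rate after recurrence. The chance of at least 4 visits is 1 − e^(−μ)(1 + μ + μ²/2 + μ³/6):

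- m = 0: μ = 1, 1 − 0.368 × 2.667 = 0.02
- m = 0.5: μ = 2.5, 1 − 0.0821 × 9.229 = 0.24
- m = 1: μ = 4, 1 − 0.0183 × 23.67 = 0.57
- m = 2: μ = 7, 1 − 0.000912 × 89.67 = 0.92

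A patient who never recurs has μ = 2 × 2 = 4, hence 0.57. Group membership is unrelated to recurrence only at m = 1.

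**Step 2: recurrence curve for the simulation.** The Protocol gives 40% at 1 year with conventional follow-up (Expected outcomes) and 60% at 3 years (Resume). Joining the two and applying them to the whole cohort is an assumption.

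- Year-1 hazard: −ln(0.60) = 0.511
- Years 1 to 3: −ln(0.40/0.60)/2 = 0.203 per year
- 2-year risk: 1 − 0.60 × e^(−0.203) = 0.51

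**Step 3: simulation with no true effect.** n = 158. Visits average 2 per year with gamma variation between patients (shape 3, assumed). Groups are formed by at least 4 visits over the full 2 years.

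| Visit rate after recurrence | Recurrence, experimental vs control | Hazard ratio | Fisher rejects |
|---|---|---|---|
| Stops | 19% vs 64% | about 0.18 | 100% |
| Halves | 38% vs 59% | about 0.51 | about 67% |
| Falls by a quarter | – | about 0.74 | about 20% |
| Unchanged | 51% vs 51% | about 1.0 | about 4% |
| Doubles | 60% vs 37% | about 2.1 | about 79% |

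As a rough check on the first row, the ratio of cumulative hazards is ln(0.81)/ln(0.36) = 0.21, close to the fitted value.

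**Step 4: different assumptions.** Constant hazards give a 2-year risk of 45.7% (from 60% at 3 years) or 64% (from 40% at 1 year). All patients have the same visit rate of 2 per year; 1000 studies per scenario. Results are in that order.

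- Stops: hazard ratio 0.21 / 0.21; log-rank rejects 100% / 100%
- Halves: 0.45 / 0.47; 93% / 96%
- Falls by a quarter: 0.68 / 0.70; 40% / 43%
- Unchanged: 1.00 / 1.01; 4.6% / 4.3%
- Rises by half: 1.87 / 1.88; 70% / 77%
- Doubles: 3.28 / 2.93; 98% / 99%

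The direction in each scenario is the same; the size moves with the assumptions.

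**Step 5: comparison with the hoped-for effect.** 25% vs 40% at 1 year corresponds to ln(0.75)/ln(0.60) = 0.56. Halving attendance after recurrence gives 0.45 to 0.51 with no effect at all.

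**Step 6: do the alternatives remove it?** With visits stopping at recurrence, a time-dependent exposure switched on at the second pre-recurrence visit gave a hazard ratio of 1.02 and 4.5% rejections. Under the Step 4 assumptions, a 12-month landmark gave 26.3% vs 26.1% and 40.0% vs 39.9%, with log-rank rejections of 5.4% and 4.7%. About 117 or 95 of the 158 patients remained.

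**The case against.** The strongest reply is that the bias is conditional and the protocol does not show that its condition is met. Much of this stands.

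- **Size.** A reader might infer that the false-positive rate must be far from 5%. The documents do not support that. With attendance unchanged, Fisher rejects about 4%. In the Step 3 model, a change of 10% downwards or upwards gives 4% or 6%. Severe inflation needs a substantial change in attendance, and the protocol gives no figure for one.
- **Immortal time.** A reader might also infer that early recurrences fall into the control group by construction. Inclusion requires 2 years of post-healing follow-up, and nothing says that counting stops at recurrence, so a patient who recurs early can still reach 4 visits. Strict immortal time arises only if visits stop, or are not counted, after recurrence.
- **Cox model.** Its follow-up term is not worded as the 4-visit group, the model is conditional, and its coding could be set out in a statistical analysis plan not shown. But the protocol describes a yes/no term without time-dependent handling. Adjusting for patient characteristics does not repair an exposure that may use later visits. Nor do pedicure care and footwear, which are themselves recorded during follow-up.

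The core is not answered. The grouping rule and the Fisher and log-rank comparisons are fixed in the protocol, so this is not a detail left for later. The observational design does not excuse it either, since the primary objective is to evaluate benefit.

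**Conclusion.** The plan is wrong as written and should be changed before data extraction. Exposure and outcome share one 2-year window, and nothing in the protocol stops group membership from depending on events after recurrence. The comparisons are biased towards benefit if counted attendance falls after recurrence, towards harm if it rises, and free of this bias only if it does not change. The net direction is unknown.

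The simulated hazard ratios with no true effect run from about 0.2 (visits stop) to between 2 and 3 (visits double). They rest on assumed visit patterns and an assumed recurrence curve and show what is possible. They do not predict the result of this study. That direction follows attendance does not depend on those figures.

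**What to change.** 1. **Nature of data collected:** extract the dates of healing, each honoured consultation, first recurrence and last contact. The list now names only the number of visits.
2. **Description of the statistical methods:** base the test of benefit on a Cox model with time-dependent exposure. Each patient starts unexposed at healing, and exposure is updated from past, pre-recurrence visits only. The rule should reflect the 2-per-year rhythm, for example at least 2 honoured visits in the preceding 12 months. A second visit at any time is too loose: in the Step 3 visit model, 26% of patients so exposed have that visit after month 12.
3. **Sensitivity analysis:** a 12-month landmark. Take patients recurrence-free at 12 months, group them by at least 2 vs fewer visits in months 0 to 12, and compare recurrence over months 12 to 24.
4. **Fixed 2-year grouping:** if kept, report it as description only, with no test or claim of benefit. Do not combine it with a count limited to pre-recurrence visits, which would recreate the worst case of 19% vs 64%.

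The cost is rewording and extraction of dates from the same medical records. The landmark drops first-year recurrences, which is why it is not the main analysis.

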###### DATA MANAGEMENT

- 1. **Data collection methods**

The data will be collected retrospectively, via the computerized medical records, on the Reference software.

###### Data flow and confidentiality protection method

- - 1. **Flow**

Data will be collected by the investigating team in a pseudo-anonymized manner in a password protected Excel file hosted on the hospital network

###### Nature of data collected

- Verification of inclusion criteria

- Age and gender

- Type and duration of diabetes

- Presence of arterial disease, diabetic neuropathy

- History of amputation

- HbAlC

During the 2-year observation period from the date of recovery:

- Number of follow-up visits honored over a two-year period from the time of healing

- Recurrence of foot wounds Hospitalization for foot wounds

- Pedicure follow-up

- Appropriate footwear.

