#### Secondary outcomes

- Hospitalization for foot wound at 2 years
- Pedicure follow-up at 2 years
- Wearing suitable footwear at 2 years
  1. Type of study

Monocentric retrospective cohort study, observational study.

9/î4

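### The data list records no characteristic of the index foot wound and the Cox model omits the collected amputation history, so confounding by wound severity is only partly controlled

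*Protocol*

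**What the plan says.** The protocol describes a "Monocentric retrospective cohort study, observational study". Patients enter through one event: "Discharge from hospital from a foot wound between 2017 and 2019 with a 2 years post-healing follow-up". Under Conduct of the research, "The 2 groups will be defined according to the number of consultations honored each year over a 2-year period"; those with at least four kept visits in two years form the experimental group and all others the control group.

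Under Nature of data collected, the baseline items are "Verification of inclusion criteria", age and sex, diabetes type and duration, HbA1c, "Presence of arterial disease, diabetic neuropathy" and "History of amputation". Visits, recurrence, hospitalisation, pedicure and footwear are then recorded "During the 2-year observation period from the date of recovery".

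Under Description of the statistical methods, the rates are compared by Fisher tests and the recurrence times by a log-rank test, all unadjusted. If its conditions are met, a Cox model is fitted "taking into account the characteristics of the patients (age, sex, length of diabetes, presence of arterial disease, neuropathy"), together with follow-up group, pedicure and footwear.

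**The concern.** Groups formed by attendance can differ in risk before follow-up starts. The severity of the healed wound could plausibly affect both sides: how often a patient is recalled or is able to attend, and whether the foot breaks down again. The Cox model is the only planned analysis that separates follow-up from patient risk, so what it leaves out stays in the estimate of benefit.

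Two gaps follow from the text. The wound itself is not described in the data list. Amputation history, the nearest collected marker of past severity, is not in the model. The second gap can be closed at analysis. The first cannot, because extraction will be over; closing it later means reopening every record.

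**Working it through.** **Text check.** The data list and the Cox list, side by side:

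| Item | Collected | In Cox model |
|---|---|---|
| Arterial disease, neuropathy | yes | yes |
| Amputation history | yes, not tied to the index wound | no |
| HbA1c | yes | no |
| Index wound led to a hospital discharge | yes (eligibility check) | not applicable |
| Healing date | implied by the start of observation | as time origin only |
| Depth, infection or bone involvement of the index wound | no | no |

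The protocol gives no figure for this bias, so there is none to reproduce.

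**Reference effect.** The protocol expects about 25% recurrence at one year with the follow-up and 40% without. Under proportional hazards the implied hazard ratio is ln(0.75)/ln(0.60) = 0.56. The risk ratio is 0.25/0.40 = 0.625.

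**Size of the bias (all inputs assumed; the documents give none).** No true effect; 40% severe wounds; group fixed at baseline; no proxy in the model. Let a1 and a0 be the share of severe and other patients who reach four visits. The severe share is then:

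- experimental: q1 = 0.4·a1 / (0.4·a1 + 0.6·a0)
- control: q0 = 0.4·(1−a1) / [0.4·(1−a1) + 0.6·(1−a0)]

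With g the hazard ratio for severity, the spurious ratio is approximately (1 + q1(g−1)) / (1 + q0(g−1)).

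| a1 / a0 | q1 | q0 | g = 1.5 | g = 2 | g = 3 |
|---|---|---|---|---|---|
| 0.70 / 0.40 | 0.28/0.52 = 0.538 | 0.12/0.48 = 0.250 | 1.13 | 1.23 | 1.38 |
| 0.60 / 0.40 | 0.24/0.48 = 0.500 | 0.16/0.52 = 0.308 | 1.08 | 1.15 | 1.24 |
| 0.40 / 0.60 | 0.16/0.52 = 0.308 | 0.24/0.48 = 0.500 | 0.92 | 0.87 | 0.81 |
| 0.35 / 0.60 | 0.14/0.50 = 0.280 | 0.26/0.50 = 0.520 | 0.90 | 0.84 | 0.76 |

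For example, the last cell is (1 + 0.28·2)/(1 + 0.52·2) = 1.56/2.04 = 0.76.

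Simulated Cox fits (60,000 patients per scenario, baseline hazard 0.35 per year, censoring at 24 months) agree closely:

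- g = 1.5: roughly 0.90-0.94 or 1.06-1.14
- g = 2: roughly 0.84-0.89 or 1.10-1.22
- g = 3: roughly 0.76-0.82 or 1.22-1.35

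**Effect of proxies.** With one measured proxy in the model, assumed 75% sensitive and 75% specific for severity, the g = 3 results shrink from 0.76 to 0.81 and from 1.33 to 1.25.

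**Comparison with the reference effect.** The most favourable scenario gives ln(0.76)/ln(0.56), a little under half of the expected log effect. Only a much stronger imbalance comes close: 20% severe in the experimental group against 60% in control, with a risk ratio of 3 for severity, gives 1.4/2.2 = 0.64 against the expected 0.625.

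**The case against.** Unmeasured severity is a general limit of retrospective cohorts, and no sentence of the protocol is wrong here. Arterial disease and neuropathy are adjusted for, amputation history is collected, and restricting entry to hospitalised wounds may narrow the range of severity. Every input to the size is assumed. The Cox model is conditional, so the fix leaves the Fisher and log-rank comparisons untouched. All of this stands. It limits the weight of the point without removing it, because the two lists are fixed in the protocol and the extra item is cheap only before extraction.

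Three stronger readings are tempting, and the documents do not support them.

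- **That nothing about the index wound is known, so severity confounding is wholly uncontrolled.** Eligibility confirms a hospitalised wound, the healing date is implied, and partial proxies are collected, two of them modelled.
- **That severity alone could account for the expected benefit.** In the scenarios above it does not, and the documents do not show which way the bias runs; it could as easily hide a benefit.
- **That adding severity gives an unbiased hazard ratio.** In the simulation it returns 0.98-1.01, but only because the group is fixed at baseline. The protocol counts visits over the same two years as recurrence. In a null simulation in which follow-up visits stop at recurrence (an assumption), the severity-adjusted hazard ratio was still about 0.22.

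**Conclusion.** The point holds in limited form. As written, the plan controls for index-wound severity only indirectly, through arterial disease and neuropathy, and leaves one collected marker unused. Under the stated assumptions the residual distortion runs from about 6-14% either way when severity has a modest effect (hazard ratio 1.5) to about 18-35% when it has a strong one (hazard ratio 3), before any shrinkage from proxies. Its direction is unknown. It would shift the adjusted estimate materially without by itself producing the expected 0.56. The change is worth making before data collection, but it deals with measured confounding only, and the adjusted hazard ratio should not be described as unbiased on the strength of it.

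**What to change.** - **Nature of data collected:** add one defined index-wound severity variable read from the index-stay record, for example deep or bone infection documented (yes / no / not recorded).
- **Description of the statistical methods:** add that variable and the already collected amputation history to the Cox model as baseline covariates.
- **Optional, for description only:** time from discharge to healing. It leaves out the inpatient period, so a severe wound kept longer in hospital could show a short interval. It is too weak a marker to serve as the adjustment variable.
- **Reporting:** state that residual severity confounding remains possible, and make no claim that this adjustment corrects for defining the groups by visits during the outcome window.

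The cost is one extra column, from records already opened to check eligibility, and two model terms (one more coefficient if not recorded is kept as its own level), with a slightly wider confidence interval. The model goes from 8 to 10 terms. If the expected one-year rates continue at a constant hazard (an assumption), 158 patients would give between 158 × (1 − 0.75²) = 69 and 158 × (1 − 0.60²) = 101 recurrences in two years, or about 7 to 10 per term. The count should be checked against the actual events before fitting. No new patients or procedures are needed.

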#### Secondary objectives

Evaluate the benefit of a specific multidisciplinary follow-up of the healed diabetic foot at the rate of 2 annual consultations on :

- recurrence with the need for hospitalization.
- pedicure follow-uo of patients.
- wearing suitable footwear.

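### Pedicure care and adapted footwear are not recorded at healing, so the unadjusted 2-year comparisons can show an association with attendance but not the benefit named in the secondary objectives

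*Protocol*

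**What the plan says.** The Protocol's Secondary objectives section sets out to "Evaluate the benefit of a specific multidisciplinary follow-up of the healed diabetic foot at the rate of 2 annual consultations on" three things, two of which are pedicure follow-up and suitable footwear. The matching Secondary outcomes are "Pedicure follow-up at 2 years" and "Wearing suitable footwear at 2 years".

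Nature of data collected first lists patient characteristics: age, gender, type and duration of diabetes, arterial disease, neuropathy, amputation history and HbA1c. A second block opens with "During the 2-year observation period from the date of recovery". Pedicure follow-up and footwear appear only in that second block, together with recurrence, hospitalization and the visit count, "Number of follow-up visits honored over a two-year period from the time of healing". No section asks for either item at the date of healing.

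On the groups, Conduct of the research states: "The 2 groups will be defined according to the number of consultations honored each year over a 2-year period". At least 4 consultations over 2 years places a patient in the experimental group, and fewer places the patient in the control group. Description of the statistical methods then states: "The rates of recurrence, hospitalization, pedicure follow-up and adapted footwear will be compared between the 2 groups by Fisher exact tests". The only adjusted model in that section is the Cox regression for time to recurrence. There the two items enter as covariates ("whether they had pedicures and whether they wore adapted shoes") and not as outcomes.

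**The concern.** Every eligible patient has been discharged after a foot wound and has then healed. Some may plausibly have a podiatrist and adapted shoes already on the day follow-up starts. The protocol does not say how many, or whether they are more common among patients who later keep their appointments.

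If they are more common there, the two groups differ at time zero. An unadjusted comparison of 2-year rates carries that difference through to the result. The report could then present as a benefit of the consultations something that was in place before the first one. Two of the three secondary objectives are exposed to this. The primary outcome is not a pedicure or footwear rate, so this particular gap does not touch it.

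The gap lies in the protocol's own data list. A SAP can choose a method of adjustment, but it cannot adjust for a status that nobody extracted.

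**Working it through.** No figure in the protocol is at stake, so there is nothing to reproduce. The check has two parts.

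**1. Setting the sections side by side**

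| Element | What the protocol fixes |
|---|---|
| Objective | Benefit of follow-up on pedicure care and on footwear |
| Outcome | Status at 2 years |
| Exposure | Visits honored during the 2 years after healing, threshold 4 |
| Status at healing | Not listed for either item |
| Analysis of these outcomes | Fisher exact test, no adjustment stated |

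A benefit is a change in the 2-year status caused by follow-up. Where the patients choose the exposure, the observed difference in 2-year rates combines (a) any effect of follow-up, (b) differences already present at healing and (c) other differences between attenders and non-attenders. The listed data give no means of separating (a) from (b).

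**2. Illustration of size**

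From the protocol: 158 patients (summary table); two-sided tests at 5% (Description of the statistical methods). Assumed, because the protocol gives neither: the group split and the prevalence at healing. Also assumed: follow-up has no effect, and each patient's status at healing carries over to 2 years.

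*Single tables, 158 / 2 = 79 per group, two-sided Fisher test:*

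- 47/79 = 59.5% against 32/79 = 40.5%: difference 15/79 = 19.0 points, p = 0.026.
- 46/79 = 58.2% against 33/79 = 41.8%: difference 13/79 = 16.5 points, p = 0.056.
- 43/79 = 54.4% against 35/79 = 44.3%: difference 8/79 = 10.1 points, p = 0.27.

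*Chance of a significant result.* Let X1 ~ Bin(n1, p1) and X2 ~ Bin(n2, p2) be the numbers with the item in each group. The chance is the sum of P(X1 = i) × P(X2 = j) over all tables (i, j) with Fisher p ≤ 0.05.

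| Rates at healing (assumed) | 79/79 split | 53/105 split |
|---|---|---|
| 50% v 50% | 3.1% | 4.3% |
| 55% v 45% | 18.6% | 20.1% |
| 60% v 40% | 64.8% | 64.1% |
| 65% v 35% | 95.4% | 94.4% |

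With an even split, a 10-point imbalance at healing multiplies the false-positive rate by 18.6 / 3.1 = 6. The uneven split gives much the same picture.

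**The case against.** A reader might infer that the two objectives cannot be answered at all. The documents do not support that. The outcomes are defined at 2 years, the rates will be collected, and an association with attendance can be estimated. Only the causal reading fails. Nor does the protocol exclude information from the day of healing: the observation window opens on that date and the records exist. What is missing is an explicit item.

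A reader might also infer that anyone equipped at healing counts automatically as a success at 2 years. The footwear outcome is worded as wearing at 2 years, so a patient who has stopped would not count. Helping patients keep an existing habit is a legitimate effect of follow-up, and new uptake is not the only target worth measuring. This stands, and it is why a comparison limited to patients without the item at healing should not be the main analysis.

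The missing status at healing is not the only source of bias. Attendance is self-selected and counted over the same 2 years as the outcomes. Motivation and access may drive both, and two extra fields would reduce the bias without removing it. This also stands.

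The size is hypothetical. No section shows that attenders are better equipped at healing, and the single-table results are fragile: moving one patient in each group takes p from 0.026 to 0.056.

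Finally, the data list is short, and field-level detail could sit in a collection form that is not shown. However, the list does separate patient characteristics from items of the observation period, and it puts both of these in the second block. The protocol as written therefore does not secure the status at healing.

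**Conclusion.** The point holds in a limited form. The protocol asks for no status at healing for pedicure care or footwear, and it compares their 2-year rates without adjustment between groups that patients form by their own attendance. A difference present at healing cannot be told from an effect of follow-up, so these two secondary comparisons support an association and not the stated benefit.

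The size is unknown. Under the assumptions above, a starting difference of 10 points produces a false-positive result in about 19% to 20% of studies, and one of 20 points in about 64% to 65%. With equal rates at healing the test behaves properly (3.1% to 4.3%). These figures show what could happen and do not estimate what will.

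The change is worth making because it is cheap, but it will not turn the comparison into evidence of causation.

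**What to change.** 1. In Nature of data collected, add two items to the patient characteristics, taken from the same records: pedicure follow-up at the date of healing (yes/no) and adapted footwear at the date of healing (yes/no).
2. In Description of the statistical methods, compare the 2-year rates adjusted for or stratified by status at healing, for example by logistic regression with group and status at healing as terms. Give the comparison among patients without the item at healing as a sensitivity analysis only.
3. Do not add a rule that counts only items started before the first recurrence. It would make these outcomes depend on the primary outcome: patients who recur early would have less time to qualify, so a group difference in recurrence could by itself create a difference in footwear or pedicure care.
4. Reword the two secondary objectives, in the summary and in the Secondary objectives section, as associations between attendance and status at 2 years. State that self-selected attendance over the same window leaves residual bias. If status at healing proves unrecoverable, this rewording is the minimum.

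Cost: two fields in the Excel file, filled from records already being read, and wording changes in the sections named. Some values at healing will be missing and should be reported by group, and the sensitivity analysis will use fewer patients.
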